### **5.3.4 Randomization:**

This study is a parallel, randomized, controlled study, Patient will be randomized by the predesigned randomization schedule using randomization envelope.

### **5.3.5 Criteria for Subject Withdrawal**

Subjects are free to discontinue the trial at any time without giving their reasons.

A subject must be withdrawn in the event of any of the following:

1. Withdrawal of the subject's consent.
2. Occurrence of an exclusion criterion which is clinically relevant and affects the subject's safety, if discontinuation is considered necessary by the Investigator.
3. Intolerance to Concor® treatment.
4. Occurrence of unexpected adverse events that are unacceptable in nature, severity and/or duration, or the frequency of known unacceptable adverse events is higher than expected.

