## **7.1 Trial procedures and assessments**

### **7.1 Trial schedule and assessment contents**

The trial procedure and assessment contents are as follows:

1. Visit 1 -Week -1 (1 +3 day): this visit entails the following:

Before any procedures that are related to the trial is undertaken, informed consent of the patient should be obtained. Thereafter, basic information of the patient will be obtained and patients are screened for eligibility based on the inclusion and exclusion criteria.

- ①. Record birth date, gender, height, weight, waist circumstance, current medical condition and past medical history, including concomitant therapies.
- ②. Perform physical examinations, including vital signs (blood pressure, heart rate).
- ③. Blood tests: full blood count (white blood cells, neutrophils, red blood cells, hemoglobin and platelets), liver function (ALT, AST), renal function (Bun, Cr), fasting blood glucose and blood lipids (TC, TG, LDL-C and HDL-C).
- ④. 12-Lead ECG and echocardiography

- ⑤. Sepical tests: central blood pressure, BRS, BPV, HRV, Holter and 24 h-ABPM
2. Visit 2-Week 2 (14+3 days): this visit entails the following:
- ①. Perform physical examinations, including vital signs (blood pressure, heart rate), 12-Lead ECG.
  - ②. If the RHR is lower than 65 bpm, test BRS, BPV, HRV. Remain the treatment for an extended 2-week, then go for Last visit.
  - ③. Record AE and concomitant therapies.
3. Visit 3-Week 4 (28 +3 days): this visit entails the following:
- ①. Perform physical examinations, including vital signs (blood pressure, heart rate), 12-Lead ECG.
  - ②. If the RHR is lower than 65 bpm, test BRS, BPV, HRV. Remain the treatment for an extended 2-week, then go for Last visit.
  - ③. If the RHR is still higher than 65 bpm, adjust the dosage of bisoprolol or atenol according to blood pressure and heart rate. After 2 weeks, go for Visit 4.
  - ④. Record AE and concomitant therapies.
4. Visit 4-Week 6 (42+3 days): this visit entails the following:
- ①. Perform physical examinations, including vital signs (blood pressure, heart rate), 12-Lead ECG.
  - ②. If the RHR is lower than 65 bpm, test BRS, BPV, HRV. Remain the treatment for an extended 2-week, then go for Last visit.
  - ③. If the RHR is still higher than 65 bpm, directly go for Last visit.
  - ④. Record AE and concomitant therapies.
5. Last Visit- End of extended treatment:
- ①. Perform physical examinations, including vital signs (blood pressure, heart rate), 12-Lead ECG.

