### **8.3 Endpoints**

#### **8.3.1 Primary Endpoint(s)**

The primary endpoint is BRS and central blood pressure at Last visit.

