## **10.2 Source Data and Subject Files**

Detailed procedure should comply with the ICH-GCP guidelines, management regulations of the clinical trial and applicable regulations of local hospital.

The Investigator must keep a subject file (medical file, original medical records) on paper or electronically for every subject included in the trial. This file will contain the available demographic and medical information for the subject, and should be as complete as possible. In particular, the following data should be available in this file:

1. Subject's full name,
2. Date of birth,
3. Gender,
4. Medical history and concomitant diseases,
5. Concomitant therapies (including changes during the trial),
6. Date of subject's inclusion into the trial (i.e. date of giving informed consent),
7. Dates of the subject's visits to the site,
8. Any medical examinations and clinical findings predefined in the protocol,
9. All adverse events observed in the subject,
10. Date of subject's end of trial, and
11. Date of and reason for early withdrawal of the subject from the trial or from Investigational Medicinal Product, if applicable.

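### Patients withdrawn under section 5.3.5 before the Last visit have no planned end assessment, so their primary endpoint is missing by design, and the intolerance criterion names one arm's drug only

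*Protocol*

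**What the plan says.** Protocol section 5.3.5 introduces its list with "A subject must be withdrawn in the event of any of the following". Four items follow:

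1. Withdrawal of consent.
2. Emergence of a clinically relevant exclusion criterion affecting safety, where the investigator judges that stopping is needed.
3. A tolerability criterion, which reads "Intolerance to Concor® treatment".
4. A criterion for adverse events, met when they are both unexpected and unacceptable, or when known unacceptable ones occur more often than foreseen.

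Section 8.3.1 reads "The primary endpoint is BRS and central blood pressure at Last visit". Section 7.1 heads that visit "Last Visit- End of extended treatment" and gives a second route to it from Visit 4: "If the RHR is still higher than 65 bpm, directly go for Last visit".

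Section 10.2 asks the subject file to hold "Date of and reason for early withdrawal of the subject from the trial or from Investigational Medicinal Product, if applicable", so it treats leaving the trial and leaving the drug as two different events.

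Section 8.4.1 makes all subjects with at least one dose the main set, labelled ITT, for all efficacy evaluations. Section 8.5.1 treats premature discontinuers as missing and removes them from the analysis.

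**The concern.** Items 2 to 4 concern tolerability and drug effect, yet they carry the same consequence as withdrawn consent. No procedure is described for a patient who comes off study drug but would agree to be measured.

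The resulting loss is unlikely to be random. Bradycardia and hypotension are exclusion criteria in section 5.3.3, so under item 2 a strong haemodynamic response can itself lead to withdrawal. The endpoints are haemodynamic too. Item 3 names bisoprolol's brand only. Intolerance to atenolol has to enter through item 2, which is discretionary, or item 4, which is limited to unexpected events or an excess of known ones. On the text itself, mandatory withdrawal can therefore differ between arms.

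This is a gap in data collection, separate from the rule in section 8.5.1. If that rule alone were corrected, there would still be no measured central pressure to analyse. No analysis plan can supply measurements that were never taken. The end-of-study blood tests, Holter and 24-hour ABPM are also unscheduled for these patients.

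**Working it through.** **What is measured, and when (section 7.1)**

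| Visit | Central blood pressure | BRS |
|---|---|---|
| Visit 1 | yes | yes |
| Visits 2, 3, 4 | not listed | only if resting heart rate is below 65 bpm |
| Last visit | yes | yes |

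**Routes to the Last visit**

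- From Visit 2, 3 or 4 with heart rate below 65 bpm: two more weeks of treatment, then the Last visit.
- From Visit 4 with heart rate still above 65 bpm: directly to the Last visit.
- From withdrawal under section 5.3.5: none described.

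Take a patient withdrawn in week 3. There is no planned central pressure on treatment. BRS on treatment exists only if heart rate was already below 65 bpm at Visit 2. The endpoint defined at the Last visit is absent in either case.

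**Size**

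The protocol states 110 patients at 1:1, hence 55 per arm. It gives no effect size, SD, power or stopping rate, so the 110 cannot be reproduced. Every rate and gap below is an assumption.

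*Precision.* With two-sided alpha 0.05 (sidedness is not stated) and 80% power, the detectable difference is (1.960 + 0.842) × sqrt(2/55) = 0.534 SD. Equal loss in both arms gives, for that same difference:

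| Assumed loss | Left per arm | Power |
|---|---|---|
| 5% | 52 | 77.8% |
| 10% | 49 | 75.3% |
| 15% | 46 | 72.6% |
| 20% | 44 | 70.7% |

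*Bias.* Let p be the proportion lost in an arm and g the gap in mean outcome between completers and stoppers, in SD, taken as the same in both arms. The completers' mean then differs from the full arm's mean by p × g, so the arm comparison shifts by (pA − pB) × g.

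- 15% vs 5%, g = 0.5: 0.10 × 0.5 = 0.05 SD.
- 15% vs 5%, g = 1.0: 0.10 × 1.0 = 0.10 SD.
- Equal loss: zero.

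At 15% vs 5% there are 46 and 52 completers, and the standard error of the difference is sqrt(1/46 + 1/52) = 0.202 SD. The ratios are 0.05/0.202 = 0.25 and 0.10/0.202 = 0.49.

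**The case against.** A reader might infer that section 5.3.5 turns every stop of study drug into withdrawal from the trial. It does not say so. The triggers are limited, item 2 rests on the investigator's judgement, and nothing forbids stopping drug while staying in. Section 7.4.1.2 records drug withdrawal as an action taken after an adverse event, and section 10.2 separates the two statuses.

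A reader might also infer that the Last visit exists only after extended treatment, or that these patients never have any primary measurement. The direct route from Visit 4 contradicts the first. Interim BRS in patients below 65 bpm limits the second, which holds only for the endpoint as timed and for central pressure after baseline.

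Three further objections carry some weight:

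- The background frames the question as one in patients with controlled heart rate, so the value of measurements off drug is open to debate. That argues for choosing deliberately, but section 8.4.1 already promises all treated subjects.
- Serious adverse events are followed until stable or the outcome is known (section 7.4.1.3), and section 7.4.3 allows further laboratory tests on clinical need. Neither provides BRS or central pressure.
- The study-flow and dose-adjustment figures are not visible and might show an early-stop assessment. The written schedule, which lists each visit's tests, does not.

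**Conclusion.** The point holds for patients withdrawn under items 2 to 4 of section 5.3.5 before reaching the Last visit. They have no planned primary endpoint value, section 8.5.1 then removes them, and the population promised in section 8.4.1 cannot be analysed as defined. The one-arm wording of item 3 allows this loss to differ by treatment.

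The size is uncertain because the protocol gives no stopping rate. Under a 10-point difference in loss and a gap of 0.5 to 1.0 SD, the shift is 0.05 to 0.10 SD, roughly 0.25 to 0.5 of a standard error. Extreme inputs (20% vs 5%, gap 1 SD) give 0.15 × 1 = 0.15 SD. With 44 and 52 completers the standard error is sqrt(1/44 + 1/52) = 0.205, a ratio of 0.73. A reader might take that as the expected bias, but nothing in the protocol supports those inputs over an observation of one to two months. The direction is also unknown.

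**What to change.** - **Section 5.3.5:** separate stopping study drug from leaving the trial, as section 10.2 already does, so that only withdrawal of consent ends data collection. The wording of item 3 must be reconciled for the two arms. When and why treatment is stopped stays with the sponsor and investigators.
- **Section 7.1:** extend the Last visit heading to cover early stopping of study drug. Perform the existing Last-visit tests then if the patient is willing, and record the date and the time since last dose.
- **Section 8.5.1:** amend it so that these values enter the section 8.4.1 analysis instead of being dropped.

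The cost is a short amendment, and it brings forward a visit already planned for each patient. It has to be in place before patients stop. The downside is small: some values come after shorter exposure or shortly after the last dose, which the recorded dates make visible. The change therefore reduces the loss without fully recovering the endpoint at its scheduled time.

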## 5. Study Design

### 5.1 Study Design

It is a single-centers, randomized study in China, and planned to enroll 110 essential hypertension patients from 1 sites, who will be assigned to two groups randomly. All the inclusive patients will be consistent with the diagnosis of essential hypertension, and have a resting heart rate(RHR)  $\geq 70$  beats per minutes(bpm).

The inclusive patients will be assigned to two groups as follow (ratio 1:1)

Arm A: bisoprolol, 5-10mg/day for a targeting heart rate of less than 65 bpm(96)

Arm B: atenolol, 50-100mg/day for a targeting heart rate of less than 65 bpm (96)

The patient will receive bisoprolol 5mg Qd.(or atenolol 25mg Bid) for 2 weeks. If his/her heart rate<65bpm, this initial dose will be prolonged for another 2 weeks before the observation is over.

If the heart rate>65bpm, the patient will receive bisoprolol 7.5mg Qd.( or atenolol 37.5mg Bid) for 2 weeks. Then if his/her heart rate<65bpm, this increased dose will be prolonged for another 2 weeks before the observation is over.

If the heart rate>65bpm, the patient will receive bisoprolol 10mg Qd.( or atenolol 50mg Bid) for 2 weeks. Then if his/her heart rate<65bpm, this increased dose will be prolonged for another 2 weeks before the observation is over. If the heart rate>65bpm, the observation is over directly.

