### **5.3.3 Exclusion Criteria:**

- Atrial Fibrillation (AF)/ Sick Sinus Syndrome (SSS)/ atrioventricular block 2-3 grade(AVBII -III ) without pacemaker
- Bradycardia
- hypotensive
- Unstable Angina Pectoris (UAP)/AMI/ HF (NYHA class III - IV)
- Uncontrolled diabetes mellitus (DM)
- Bronchial asthma
- Gastro-intestinal ulcer or skin ulcer
- Liver dysfunction/ renal impairment
- Treated with CCB (Calcium antagonists) ( except amlodipine) or other beta blocker.
- Glaucoma
- Known allergic/ intolerance to beta blocker
- Pregnant or lactating women
- Participation in another clinical study within the last 3 months
- Legal incapacity or limited legal capacity

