### **6.3 Non-permitted Medicines**

CCB, ACEI, ARB, diuretics and  $\beta$ -blockers other than Concor® are not permitted during the trial.

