3. BRS
4. BPV
5. HRV

## 7.4 Assessment of Safety

### 7.4.1 Management and reporting of adverse events

#### 7.4.1.1 Definitions

##### *Adverse Event*

An adverse event (AE) is any untoward medical occurrence in a subject or clinical investigation subject administered a pharmaceutical product, which does not necessarily have a causal relationship with this treatment.

An AE can therefore be any unfavorable and unintended sign (including an abnormal laboratory finding), symptom, or disease temporally associated with the use of a medicinal product, whether or not considered related to the medicinal product.

Investigators must assess the severity/intensity of adverse events according to the Qualitative Toxicity Scale as follows:

**Mild:** The subject is aware of the event or symptom, but the event or symptom is easily tolerated.

**Moderate:** The subject experiences sufficient discomfort to interfere with or reduce his or her usual level of activity.

**Severe:** Significant impairment of functioning: the subject is unable to carry out usual activities.

Investigators must also systematically assess the causal relationship of AEs to Concor® using the following definitions. Decisive factors for the assessment of causal relationship of an AE to the treatments include, but may not be limited to, temporal relationship between the AE and the treatments; known side effects of treatments; concomitant medication, course of the underlying disease or impact of other treatment.

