#### **7.4.1.2 Recording Adverse Events**

All adverse events occurring during the study, whether serious or not, must be recorded in the Case Report Form (CRF), including its description, severity, duration (onset and resolution dates), causal relationship (i.e., whether the adverse event is related to the study treatment), any other potential causal factors, actions taken with the study drug (dose reduction, withdrawal...), required treatment, and outcome. In addition, for all serious adverse events, seriousness criteria must be documented and a specific safety report form must be completed.

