#### **7.4.1.3 Expedited Reporting of Serious Adverse Events**

As soon as the Investigator detects a serious adverse event, as defined above, associated with the study medication, he/she will report it within 24 hours (by e-mail, phone, or fax) to principal investigator [name].

The Investigator must promptly respond to any request for follow-up information or questions from the Sponsor. Serious adverse events occurring during the study must be monitored and followed up by the Investigator until stabilization or until the outcome is known, unless the subject is lost to follow-up. The Investigator will ensure any necessary additional therapeutic measures and follow-up procedures.

Reporting procedures and timelines for any new information on a previously reported serious adverse event (follow-up) are the same as for the original report.

Further to reporting serious adverse events to the Sponsor, the Investigator will comply with any applicable local pharmacovigilance requirements to report adverse reactions/events to national pharmacovigilance systems.

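### Mandatory withdrawal for intolerance names only Concor (bisoprolol) in a two-drug randomised trial, and the same one-drug wording appears in the prohibited-medicines rule and one adverse-event causality sentence

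*Protocol*

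**What the plan says.** Protocol section 5.1 describes two randomised arms in a 1:1 ratio, bisoprolol and the comparator ("Arm B: atenolol, 50-100mg/day"). The first of the two paragraphs numbered 8.2 repeats the ratio.

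Section 5.3.5 lets any subject leave freely, then lists four events on which withdrawal is mandatory. Two of the four matter most here:

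- Item 3 reads "Intolerance to Concor" treatment. No item names atenolol.
- Item 2 covers a clinically relevant exclusion criterion that arises during the trial and affects safety, but only "if discontinuation is considered necessary by the Investigator". The exclusion list in section 5.3.3 includes "Known allergic/ intolerance to beta blocker".

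Two other rules also name Concor alone:

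- The second section numbered 6.3 (Non-permitted Medicines) bars β-"blockers other than Concor", with no exception for atenolol.
- Section 7.4.1.1, under Adverse Event, states: "Investigators must also systematically assess the causal relationship of AEs to Concor".

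The neighbouring safety text is neutral. Section 7.4.1.2 asks "whether the adverse event is related to the study treatment", and section 7.4.1.3 makes expedited reporting depend on a serious event being "associated with the study medication".

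**The concern.** A withdrawal rule in a randomised comparison should read the same for both arms. Here one arm has an explicit, unconditional ground for stopping because of intolerance, and the other does not.

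Two things are at stake. The first is the patient: someone who cannot tolerate atenolol should have the same written protection as someone who cannot tolerate bisoprolol. The second is how withdrawals are classified. A bisoprolol patient who stops for intolerance falls plainly under item 3. An atenolol patient who stops for the same reason must be filed under item 2, item 4 or own choice. Comparing the safety and compliance of the two drugs, once heart rate is below 65 bpm, is a stated secondary objective, so the reason for leaving should carry the same label in both arms.

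The prohibited-medicines rule and the causality sentence show the same one-drug wording, so this is a pattern and not a single slip.

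**Working it through.** The protocol gives no intolerance rate and no figure to reproduce, so the check is mainly a reading of the text.

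**Step 1: what Concor means.** The text shown does not define it. Section 6.3 treats it as the one permitted β-blocker, and section 6.5 gives overdose reports for it by name. Reading it as the bisoprolol product is an inference, but a sound one.

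**Step 2: exit routes for intolerance, by arm.**

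| Route in section 5.3.5 | Arm A (bisoprolol) | Arm B (atenolol) |
|---|---|---|
| Item 3, intolerance | Mandatory, no condition | Not named |
| Item 2, exclusion criterion arising | Yes, if the investigator judges it necessary | Same |
| Item 4, unacceptable unexpected events, or known ones more frequent than expected | Yes | Same |
| Subject's own choice | Yes | Same |

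Only the first row differs. Item 2 goes a long way to fill the gap, because section 5.3.3 lists class-wide β-blocker intolerance and also bradycardia, hypotension, asthma and second- or third-degree atrioventricular block. Item 4 does not squarely cover ordinary, expected intolerance in one patient.

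**Step 3: prohibited medicines.** Sections 5.1 and 6.2 prescribe atenolol to Arm B. Section 6.3 permits no β-blocker except Concor. Taken literally, the two cannot both be followed in Arm B.

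**Step 4: causality.** The sentence in section 7.4.1.1 names Concor. The sentence after it, in the same paragraph, lists the factors for judging causality to the treatments in the plural. Sections 7.4.1.2 and 7.4.1.3 are neutral. The wording is therefore inconsistent; it is not one-drug throughout.

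**Step 5: possible size of the gap in exits.** Take 110 patients at 1:1, so 110 / 2 = 55 per arm. Assume an intolerance rate q of 5% to 10% in both arms, and a share w of intolerant atenolol patients, from one half to all, who leave by the other routes. Expected exits are 55q in Arm A and 55qw in Arm B, so the gap is 55q(1 − w).

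| q | Arm A exits | Arm B exits, w = 0.5 | Gap, w = 0.5 | Gap, w = 1 |
|---|---|---|---|---|
| 5% | 2.75 | 1.375 | 1.375 | 0 |
| 10% | 5.5 | 2.75 | 2.75 | 0 |

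Section 5.1 also prints 96 beside each arm, which does not fit a total of 110. At 96 per arm the largest gap would be 96 × 0.10 × 0.5 = 4.8. All of these rest on assumed rates.

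**The case against.** The strongest reply is that the intent is obvious and nothing turns on the wording. Much of that stands.

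- **No patient is locked in.** Item 2, item 4 and free withdrawal apply to both arms. Item 3 does not define intolerance, so applying it also takes judgement, and the contrast between mandatory and discretionary is smaller in practice than on paper.
- **No one would apply section 6.3 as a ban on Arm B's own drug.** It follows the section on concomitant therapy and is naturally read as a rule on non-study drugs. A reader might infer that every atenolol patient is a protocol deviator, to be removed from the per-protocol set. The documents do not support that: sections 5.1 and 6.2 prescribe atenolol, and section 8.4.1 leaves deviations to a medical check.
- **Adverse-event data remain comparable.** A reader might infer that causality is assessed for bisoprolol alone, so that safety cannot be compared between arms. The next sentence of section 7.4.1.1 and section 7.4.1.2 contradict this. The endpoint in section 8.3.2 is all recorded adverse events, whatever their cause, and the safety set in section 8.4.3 is defined alike for both arms.

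What does not fall is the text itself. These are operative instructions that belong in a protocol and are not left to an analysis plan. As written, one omits the comparator, one forbids it, and one sits at odds with its own paragraph.

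**Conclusion.** The point holds as a minor inconsistency, centred on item 3 of section 5.3.5. The written ground for withdrawal, and with it the label given to an intolerance withdrawal, differs by arm. Section 6.3 needs an exception for atenolol, and the sentence in section 7.4.1.1 should match the text around it.

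Because section 8.5.1 drops subjects who discontinue, a reader might go further and infer that unequal exits bias the primary comparison of baroreflex sensitivity and central pressure. The documents do not show this. They give no intolerance rate and no outcome difference for intolerant patients, and the other exit routes could close the gap entirely. Under the assumptions in the working, the expected difference is between 0 and 2.75 patients with 55 per arm.

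The verdict rests on reading Concor as bisoprolol and on the trial being randomised. The second paragraph numbered 8.2 says that no randomisation is needed. That contradicts sections 5.1 and 5.3.4 and the first 8.2, and it may point to text carried over from a one-drug study.

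**What to change.** Change three lines in the protocol:

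1. Section 5.3.5, item 3: *Intolerance to the assigned study drug (bisoprolol or atenolol)*.
2. Section 6.3, Non-permitted Medicines: prohibit *β-blockers other than the assigned study drug*.
3. Section 7.4.1.1, causality sentence: assess causality to *the assigned study drug*, in line with sections 7.4.1.2 and 7.4.1.3.

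The cost is one line of rewording in each place. No patients, visits or procedures are added.
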